### Intervention

Two peer supporters will be recruited from each cluster in the intervention arm (one male and one female). These peer supporters will be selected from volunteers who meet the specified criteria. They will receive structured training in a two-day workshop. The content of the training sessions includes: an introduction to the project, the role of the peer supporter, diabetic eye disease and DR, retinal examination for DR, communication skills, managing groups, confidentiality and behaviour change. The training team will include a certified diabetes educator.

They will receive support to retain them in the study (airtime vouchers for delivering the telephone reminders). They will also receive a weekly telephone call from the principal investigator for support. The intervention group will receive the usual care, a monthly group talk and a monthly individual telephone reminder to attend retinal examination. The key messages to be delivered in the group talk are shown in Table 1. The control group will receive the usual standard of care, which consists of ad hoc diabetes educational talks, blood sugar and blood pressure measurements during support group meetings.

**Table 1 Tab1:** Key messages to be delivered to participants

*Messages on diabetic eye disease*	
1	Diabetes causes several complications in the eye, including DR
2	DR is a progressive condition that leads to blindness if treatment is not provided in good time
3	DR has no symptoms until the advance stages
4	An eye check by an eye specialist can detect damage to the eyes before symptoms develop
5	All persons with diabetes should have their eyes checked once every year by an eye specialist, even before any symptom or poor vision develops
6	Do not wait for your vision to get worse or for any other symptom to occur before you see an eye specialist
7	If eyes are found to be normal at your eye check by an eye specialist, please continue with an eye check annually
8	If you notice any abnormality with your eyes between your clinic appointments, visit the eye specialist as soon as possible. It may not mean that you have diabetic eye disease, it may be a simple problem that requires treatment.
9	The eye check may help to determine if your sugar, blood pressure, and lipid control needs to be re-assessed. Good control of your blood sugar levels, blood pressure and cholesterol reduces the risk of diabetes-related sight loss.
10	If you are found to have DR the eye specialist will inform you about the diagnosis, and how it will be treated.
*Messages on retinal examination for DR*	
1.	Ensure you have a dilated eye examination at the eye clinic at least once a year.
2.	You do not need to have a referral note to go to the clinic. However we will give you a card to present at the clinic.
3.	At the eye clinic, your vision will be checked first.
4.	A examination for DR is different from any other type of eye examination. It is called a dilated eye examination.
5.	In this examination, the doctor puts eye drops into your eyes to dilate (widen) your pupils. This allows the doctor to have a good view of the back of the eye. Both eyes need to be examined.
6.	The examination is not painful. When the eye drops are first instilled, there may be a slight stinging sensation but this only lasts about a minute. You may feel uncomfortable because of light sensitivity and blurred vision once the pupils are dilated.
7.	Do not be afraid to ask the doctor questions about the examination or about diabetic eye disease.

### Data collection

Standardized operating procedures will be used to collect data at baseline, using approved tools in the study proposal. Demographic and anthropometric (height, weight, waist circumference) as well as blood pressure, blood sugar and visual acuity will be recorded at baseline. Study participants will be given their body mass index and blood pressure measurements in the field, at the point of data collection; where these results are abnormal, participants will be referred to a health worker. Completed questionnaires will be monitored and data entry staff will be trained to minimize errors in data entry into computerized databases. Identifiers will be removed from participant data, and all paper data will be stored in locked cabinets. Electronic data will be password protected for confidentiality. A detailed data management plan is included in the study proposal.

### Follow up

Participants in both arms will be followed up for six months to assess attendance to retinal examination. Participants who are lost to follow up will be identified at the monthly contact points with peer supporters. Three home visits will be made to trace participants who are lost to follow up. Characteristics of those lost to follow-up and reasons for loss will be evaluated.

At the end of six months two separate focus group discussions will be held with two participants from each intervention cluster in each arm (*n* = 14 for each focus group discussion) to explore the experience of the support groups with the intervention. A focus group discussion will also be held with peer supporters to explore the impact of ‘peer supporting’ on the management of their own diabetes, and their role in the health care team.

### Process evaluation

A process evaluation will be conducted using qualitative interviews and non-participant observation (Table 2). The findings of the process evaluation will be evidence on why and how the intervention worked. The following domains of the intervention will be evaluated:Whether the intervention activities are implemented as planned (fidelity).The extent to which the intervention reaches the PLWD (reach).The degree to which PLWD are exposed to the intervention package (dose).The extent to which the intervention is acceptable to PLWD and to eye care workers (acceptability).

5) The contextual factors that may have an influence on the theory of change (context).

**Table 2 Tab2:** Domains and methods for process evaluation

Source	Domain	Data collection method	Stage of the trial
Trial registers	Recruitment Retention	Registers in the trial office	Throughout the trial (*n* = 700)
Participants	Fidelity Reach Dose received Effectiveness	Participant Questionnaire 2 Focus group discussions at 6 months	At recruitment (n = 700) Three months: n = 10% pf participants in each intervention cluster(35) Six months: *n* = 10-% of participants in each cluster (35) *N* = 28
Non-participant observations by PI	Recruitment Fidelity Dose delivered Context	PI Field notes	N = 2 group meetings per intervention cluster during the trial (14)
Peer supporters (PS)	Effectiveness Reach Fidelity Dose delivered Context	PS Questionnaires PS Diary for telephone calls PS Group session report form Focus group discussion at 6 months	After training (n = 14) Through the trial (n = 14) Throughout the study (1 report form per group meeting per PS) N = 7
Eye care workers Key informants	Context	In-depth interviews	At 6 months *N* = 3 *N* = 7
Research project manager	Reach Fidelity Dose delivered	Reports	At recruitment of PS At training the PS At 3 and 6 months
Research nurse	Outcome evaluation procedures	Report	At 3 months and 6 months
Study steering committee	Context	Spreadsheet of external events that may have affected study outcomes	At 6 months

*PI* Principal Investigator, *PS* Peer supporter

### Assessment of outcome

#### Primary outcome

Rates of eye examination in each arm will be assessed in each arm at the end of six months. This outcome will be assessed by an independent and masked research nurse who will review the eye clinic records of all participants. The outcome will be recorded on the outcome evaluation form for each participant. The form contains identification details of each participant recruited into the study (name, residence, telephone number) and will thus differentiate them from other patients who are examined in the eye clinic. The form does not contain information on the intervention arm to which the patient is allocated. The project manager will receive the completed outcome evaluation forms and link the data to the participant database for each arm.

#### Secondary outcomes

These outcomes will be assessed at six months:Contextual factors that affect the effectiveness of the interventionCharacteristics of peer supporters associated with uptake of eye examinationBarriers to uptake of eye examination among PLWD.

These outcomes will be evaluated using the database for participants and peer supporters, as well as data from focus group discussions with peer supporters and in-depth interviews with eye care workers at six months.

### Statistical analysis

Baseline comparability of the two groups will be assessed to check that the important confounders and baseline characteristics that would affect uptake of eye examination are balanced between the two arms through randomisation. If the arms are found to be substantially imbalanced an appropriately adjusted logistic regression model will be used.

Study-wide pooled analysis will be conducted for the primary outcome. Missing data will be reported using standard flow charts. Repeated measures mixed models regression with adjustment for age, sex, and baseline anthropometric measures will be used to compare the two groups for the primary outcome.

Analysis will be conducted on intention-to-treat basis. Regression analysis will be used to determine the extent to which individual and support group characteristics are associated with the primary outcome. Models for comparing continuous outcomes will use linear regression while models for categorical outcomes will use logistic regression. Kaplan-Meier analysis will be used to plot the survival curves for both treatment arms. Cox regression will be used to assess the impact of the intervention on time to first eye examination. The hazard ratio will be estimated with Cox regression, adjusting for substantial baseline imbalances if appropriate. Interim analysis is not planned.

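### Two unranked adjustment rules govern the comparison of uptake, one triggered by an undefined baseline imbalance, so the primary estimate can be chosen after seeing the data

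*Protocol article*

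**What the plan says.** All the analysis text is in the Statistical analysis section of the protocol article.

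- **Balance check.** The arms are inspected to see whether "important confounders and baseline characteristics that would affect uptake of eye examination are balanced between the two arms". Uptake of the eye examination is the primary outcome.
- **Conditional rule.** "If the arms are found to be substantially imbalanced an appropriately adjusted logistic regression model will be used".
- **Unconditional rule.** For the primary outcome, the next paragraph says: "Repeated measures mixed models regression with adjustment for age, sex, and baseline anthropometric measures will be used to compare the two groups". Nothing here depends on observed balance.
- **Model class.** Further on, "models for categorical outcomes will use logistic regression".
- **Time to first examination.** The Cox hazard ratio is estimated "adjusting for substantial baseline imbalances if appropriate".

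The Data collection section lists what is available for adjustment: "Demographic and anthropometric (height, weight, waist circumference) as well as blood pressure, blood sugar and visual acuity will be recorded at baseline".

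**The concern.** Both rules bear on the same comparison. If the primary model is always adjusted for a fixed list, a logistic model adjusted only when the arms look unequal is a second candidate for the same estimate. The text does not say whether it replaces the mixed model, supplements it or serves as a sensitivity analysis. Nor does it say how large an imbalance must be, or which covariates then enter.

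There are two consequences. Observed imbalance is a poor basis for choosing covariates: a variable can differ between arms by chance and have no bearing on uptake, while a balanced variable can be strongly prognostic. And because the trigger and the covariates are left to judgement once data are in hand, the headline result can be picked from at least two estimates. The protocol offers little protection against this. The Randomization section says masking is not possible and that the research team knows the allocation, and the Data monitoring section gives the principal investigator access to all trial data sets.

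**Working it through.** The plan states no figure on this point, so there is none to reproduce. Three checks follow.

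**1. The rules side by side**

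| | Conditional rule | Unconditional rule | Cox model |
|---|---|---|---|
| Model | Logistic regression | Repeated-measures mixed model | Cox regression |
| When adjusted | Only if imbalance is judged substantial | Always | Only if imbalance is judged substantial |
| Covariates | Not named | Age, sex, anthropometry | Not named |
| Threshold | None | Not needed | None |
| Outcome named | Not named, but the check concerns predictors of uptake | Primary outcome | Time to first examination |

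An analysis plan could add a threshold or a list. To reach a single primary analysis it would still have to rank or override one of these published sentences.

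**2. How often would the trigger fire by chance?**

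Inputs from the Sample size calculation section: 7 groups per arm averaging 50 members, so 350 per arm. Eight covariates are named in the Statistical analysis and Data collection sections: age, sex, height, weight, waist, blood pressure, blood sugar and visual acuity. Assumed, because not given: covariate ICC of 0.02 to 0.05, and independence of the eight.

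- Design effect DE = 1 + 49 × ICC, which is 1.98 at ICC 0.02 and 3.45 at ICC 0.05.
- SE of the standardised difference between arms = √(2 × DE / 350), which is 0.106 and 0.140 SD.
- Naive test at p<0.05 ignoring groups: p = P(|Z| > 1.96/√DE), which is 16.4% and 29.1% per covariate.
- Trigger at a difference of t SD: p = P(|Z| > t/SE).
- At least one of eight: 1 − (1 − p)⁸.

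| Reading of a substantial imbalance | At least one of eight flagged, ICC 0.02 to 0.05 |
|---|---|
| Naive test, p<0.05 | 76% to 94% |
| Difference above 0.10 SD | 97% to 99% |
| Difference above 0.20 SD | 39% to 74% |
| Difference above 0.25 SD | 14% to 46% |
| Difference above 0.30 SD | 4% to 23% |
| Difference above 0.50 SD | under 0.3% |

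For example, at 0.25 SD and ICC 0.05: 0.25/0.140 = 1.78, p = 7.5%, and 1 − 0.925⁸ = 46%. Height, weight and waist are likely to be correlated, which would lower the any-of-eight figures. A characteristic that varies only between groups behaves differently: its SE is √(2/7) = 0.535 SD, so it differs by more than 0.5 SD with probability about 0.35.

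**3. What does the freedom of choice cost?**

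An illustrative simulation under no effect used 7 v 7 groups, 42 analysed per group, uptake of 13% (assumed), one group-level covariate, ICC of the outcome from 0.01 to 0.10, and 8,000 runs per setting. The two candidates were an unadjusted and an adjusted group-level analysis. They stand in for the plan's two models and do not reproduce them. Nominal level 5%:

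| Strategy | Covariate predicts uptake (log-odds 0.3 per SD) | Covariate unrelated to uptake |
|---|---|---|
| Fixed unadjusted | 0.046–0.051 | 0.045–0.054 |
| Fixed adjusted | 0.048–0.049 | 0.046–0.053 |
| Adjust if difference exceeds a pre-stated 0.5 SD | 0.035–0.040 | 0.046–0.053 |
| Free choice of the smaller p-value | 0.066–0.076 | 0.059–0.064 |

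The excess error comes from the open choice. A mechanical trigger stated in advance does not produce it.

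**The case against.** The strongest reply is that this is a condensed article and that the threshold and covariates belong in the full protocol or analysis plan. That is fair for the missing detail. It does not answer the conflict, because both rules are printed here without ranking and the Cox sentence repeats the trigger.

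A second reply is that harm is not shown. A pre-stated trigger was at or below the nominal level, and the inflation above assumes that the better p-value is actually chosen. This stands as a limit on the size of the point. The trigger in this protocol, however, is not pre-stated.

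A reader might also infer stronger claims, which the documents do not support:

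- **That the trigger will usually fire.** This holds only under some readings, such as naive significance tests. The protocol mentions no test, and at 0.5 SD individual-level covariates would almost never set it off.
- **That the plan switches to a logistic model ignoring support groups.** The conditional sentence does not say that it replaces the mixed model, and it neither states nor excludes a cluster term.
- **That leaving out visual acuity is an error, or that anthropometry is useless.** Acuity is recorded and is not in the fixed list, but no section shows that it predicts uptake or that anthropometry does not. Any loss of precision is unquantified.
- **That prior examination is already available as a covariate.** The eligibility criteria exclude members already attending annual screening, which does not establish whether someone was ever examined. Only peer supporters must have had an earlier examination, and the Data collection section does not list the item.
- **That variables restricting the randomisation were left out of the model.** The Randomization section describes blocking only.

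**Conclusion.** The point holds as a conflict in the stated text combined with a poorly defined rule. Two unranked rules cover the comparison of uptake, one of them depends on an undefined imbalance, and the Cox model carries the same dependence. The primary estimate is therefore open to choice after the data are seen.

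The size is moderate and conditional. If the more favourable of two analyses may be reported, type I error rises from about 0.05 to 0.066–0.076 when the covariate is prognostic, and to 0.059–0.064 when it is not, under the simulation's assumed uptake, ICC and covariate effect. With 7 v 7 groups some chance imbalance is plausible, but its frequency cannot be fixed: it runs from under 0.3% to over 90% across reasonable thresholds, under the assumed ICC of 0.02 to 0.05 and independence. The plan should be corrected on this point. Nothing here undermines the design or the sample size.

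**What to change.** 1. Delete both imbalance-triggered sentences, or label those analyses as sensitivity analyses.
2. Name one primary model for the binary six-month outcome that accounts for support group. Deleting the conditional sentences is not enough, because the remaining text describes a repeated-measures model for an outcome that the Primary outcome section assesses once.
3. Fix a short covariate list now, chosen for expected prognostic value from variables already recorded at baseline: for example age and sex, with visual acuity considered as an optional addition before outcome data are seen. Include prior examination (ever/never) only if the baseline questionnaire already records it.
4. Use the same list in the Cox model.
5. Present the baseline table descriptively, with no role in model choice.

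Possible wording: *The primary analysis is the prespecified model for uptake at six months, accounting for support group and adjusted for [fixed list]. Baseline characteristics are tabulated descriptively. Further adjustment for imbalanced characteristics is a sensitivity analysis.*

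This costs a few sentences, requires no new data provided that the list keeps to recorded variables, and leaves the sample size unchanged. The Trial status section reports enrolment still under way at submission, so the change could be made before outcome data are seen if it is made promptly. What is lost is the freedom to adjust the primary result for an unexpected imbalance, which the labelled sensitivity analysis covers.

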**Methods:**

The DURE study will be a two-arm pragmatic cluster randomized clinical trial in Kirinyaga County, Kenya. Diabetes support groups will be randomly assigned to either the intervention or usual care conditions in a 1:1 ratio. The participants will be 700 PLWD who are members of support groups in Kirinyaga. To reduce contamination, the unit of randomization will be the support group. Peer supporters in the intervention arm will receive training to deliver the intervention. The intervention will include monthly group education on DR and individual member reminders to take the eye examination. The effectiveness of this intervention plus usual care will be compared to usual care practices alone. Participant data will be collected at baseline. The primary outcome is the proportion of PLWD who take up the eye examination at six months. Secondary outcomes include the characteristics of participants and peer supporters associated with uptake of eye examination for DR. Intention-to-treat analysis will be used to evaluate the primary and secondary outcomes.

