### Sample size calculation

We aim to randomize seven diabetes patient support groups (clusters) with an average membership of 50 each to each arm. The study thus has two arms of equal size (350 participants in each arm).This sample size has been calculated using standard formula for sample size for cRCTs and taking into consideration the primary outcome of interest [58, 59]. A 15% loss to follow-up contingency has been built into the sample size calculation. This sample size would have 80% power to detect a two-fold difference in the proportion of PLWD who take up eye exam, with a 5% level of significance. Member registers of the DSGs will be obtained from the team lead. These registers will be the frame for identification of participants for the study.

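### The primary comparison is described as a repeated-measures model of an outcome recorded once per person, and no arm comparison names the randomised support group

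*Protocol article*

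**What the plan says.** All references are to the protocol article.

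- **Design.** The Abstract states that "the unit of randomization will be the support group". The Sample size calculation section adds: "We aim to randomize seven diabetes patient support groups (clusters) with an average membership of 50 each to each arm".
- **Outcome.** Under Primary outcome: "Rates of eye examination in each arm will be assessed in each arm at the end of six months". A masked nurse reviews clinic records and completes one outcome form per participant.
- **Primary comparison.** Under Statistical analysis: "Study-wide pooled analysis will be conducted for the primary outcome". The same paragraph continues: "Repeated measures mixed models regression with adjustment for age, sex, and baseline anthropometric measures will be used to compare the two groups".
- **Other comparisons of the arms.** The same section plans an adjusted logistic regression if the arms turn out substantially imbalanced, and a Cox regression of time to first eye examination.
- **Support group in the analysis.** It appears only through group characteristics, examined as predictors of uptake. That is a separate question from allowing for clustering when the arms are compared.

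**The concern.** There are two faults in one sentence. First, a repeated-measures model handles several observations on the same person. Here each person contributes one, and uptake during follow-up has no baseline value, so the structure named has nothing to work on. Second, the dependence that does exist, between members of the same support group, is not mentioned in any model that compares the arms.

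The validity of the primary result is at stake. Fourteen groups are randomised, not 700 people. An analysis that takes the 700 as independent understates the standard error whenever uptake varies between groups beyond chance. Its intervals are then too narrow, and a true null is rejected too often.

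**Working it through.** **Inputs from the article.** 7 groups per arm, average size 50, 350 per arm, 15% loss to follow-up, 80% power, 5% significance (taken as two-sided), two-fold difference in proportions.

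**Assumptions.** The article states neither the control uptake nor the ICC. I take control uptake of 10 to 15% and look for the ICC that returns 350 per arm.

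**Step 1: reproduce the planned size.** For proportions p1 and p2 with mean p:

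n = [1.96·√(2p(1−p)) + 0.8416·√(p1(1−p1) + p2(1−p2))]² / (p2−p1)²

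Multiply by the design effect DE = 1 + (50−1)·ICC and divide by 0.85 for loss.

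| Assumed rates | n, no clustering | Assumed ICC | DE | n × DE | ÷ 0.85 | Without DE, ÷ 0.85 |
|---|---|---|---|---|---|---|
| 10% v 20% | 199 | 0.01 | 1.49 | 297 | 350 | 235 |
| 13% v 26% | 145 | 0.0215 | 2.05 | 298 | about 350 | 171 |
| 15% v 30% | 121 | 0.03 | 2.47 | 299 | 352 | 143 |

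The planned 350 per arm is therefore attainable, and at these rates it presupposes an ICC of about 0.01 to 0.03. Without a design effect the same rates need only 143 to 235 per arm.

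**Step 2: false-positive rate if the group is left out.** The true standard error is √DE times the one reported, so with no effect the nominal 5% two-sided test rejects with probability

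2·[1 − Φ(1.96/√DE)]

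| ICC (assumed) | DE, 50 per group | √DE | 1.96/√DE | Rejection rate |
|---|---|---|---|---|
| 0.01 | 1.49 | 1.221 | 1.606 | 10.8% |
| 0.02 | 1.98 | 1.407 | 1.393 | 16.4% |
| 0.03 | 2.47 | 1.572 | 1.247 | 21.2% |

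If 15% are lost and 42.5 per group remain, DE = 1 + 41.5·ICC = 1.415, 1.83 and 2.245, and the rates are 9.9%, 14.7% and 19.1%.

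**Step 3: simulation.** I simulated 40,000 null trials per setting: beta-binomial uptake of 10, 13 or 15%, 7 groups per arm, 50 per group.

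| ICC | Two-proportion z-test ignoring group | t-test on 14 group proportions, 12 df |
|---|---|---|
| 0.01 | 10.9–11.1% | 4.8–5.2% |
| 0.02 | 16.4–16.6% | 4.7–4.9% |
| 0.03 | 21.3–21.7% | 4.8–5.1% |

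Referring the same group-level statistic to 1.96 instead of the t value of 2.179 gives about 7%, so the small number of groups also matters.

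**Step 4: interval width.** The valid interval is wider than the one ignoring group by √DE × 2.179/1.96. With 50 per group that is 1.36, 1.56 and 1.75 times at ICC 0.01, 0.02 and 0.03.

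**The case against.** **The mixed model could carry a group effect.** Its random effects are not specified. The Design section follows the CONSORT cluster extension and wants effects at individual and cluster level, and the sample size uses a cluster formula. A full protocol or analysis plan, not shown, might fit a random effect for support group. This stands: a reader might infer that the planned p-value is certain to be wrong, and the article does not support that. It does not rescue the text, because the article goes beyond leaving detail out. It names a structure and its covariates, and that structure does not fit the outcome.

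**Pooled need not mean clustering ignored.** It may mean one analysis across all groups instead of group by group. This stands as an ambiguity, so the word needs clarifying and is not proof of error.

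**The rejection rates belong to a test the plan does not name.** They come from an unadjusted test ignoring group. They show the cost of omitting the group, not the error rate of the planned model. The rates are conditional on that omission.

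**Larger rates could be quoted.** ICCs of 0.05 and 0.10 give about 29% and 42%. At 10 to 15% control uptake those ICCs do not reproduce 350 per arm, so I do not rely on them.

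**Scale.** Powering on proportions and testing with a logistic model is routine, and the hypothesis is only directional. Reporting odds ratios is not an error here.

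**Could the outcome be repeated after all?** Table 2 lists research nurse reports at three and six months, but these concern outcome evaluation procedures within the process evaluation. They do not create a second primary measurement.

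**Conclusion.** The point holds in a bounded form. The repeated-measures description is wrong for a single binary reading at six months; this follows from the text alone. It is also plain from the text that no comparison of the arms names the support group.

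The inferential consequence is conditional. If the group is not modelled, the p-value and interval are too optimistic for any positive ICC; at an ICC of zero the problem disappears. With 50 per group, the false-positive rate is about 11 to 21% for an ICC of 0.01 to 0.03, or about 10 to 19% after the planned 15% loss. Both the ICC and the 10 to 15% control uptake are assumptions, tied to the design only in that together they return the stated 350 per arm.

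Because this concerns the primary comparison and can be settled by wording, it should be corrected before analysis.

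**What to change.** In the Statistical analysis section:

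1. Delete the repeated-measures description. Delete the pooled-analysis sentence, or say that it means one analysis across all groups with support group accounted for.
2. Name one primary analysis of six-month uptake that respects the support group. Either of these would do:
   - a mixed-effects logistic model with a random intercept for support group, a fixed effect for arm, the covariates already stated, and a small-sample correction for 14 clusters; or
   - a t-test on the 14 group proportions with 12 df.
3. Let this replace the logistic model that depends on observed imbalance, so that only one comparison of the arms on the primary outcome remains.
4. Allow for support group in the Cox model, through a shared frailty or a cluster-robust variance.

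No new data or participants are needed. The cost is a wider confidence interval than an analysis ignoring the group would give: about 1.4 to 1.7 times as wide at the ICCs above, with 50 per group.

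### The Cox, logistic and association models are named with no allowance for the randomised support groups; run as written, tests of arm or of group-level characteristics would reject too often

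*Protocol article*

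**What the plan says.** The protocol article's abstract fixes the design: "To reduce contamination, the unit of randomization will be the support group". The Sample size calculation section gives the numbers: "We aim to randomize seven diabetes patient support groups (clusters) with an average membership of 50 each to each arm". It says that a formula for cluster trials was used.

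The Statistical analysis section then names four kinds of model:

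- **Primary comparison.** A repeated-measures mixed model adjusted for age, sex and baseline anthropometry. The level of its random effect is not named.
- **Baseline imbalance.** A suitably adjusted logistic model if the arms differ substantially.
- **Time to event.** "Cox regression will be used to assess the impact of the intervention on time to first eye examination". The hazard ratio may be adjusted for substantial baseline imbalances.
- **Associations.** "Regression analysis will be used to determine the extent to which individual and support group characteristics are associated with the primary outcome". Logistic regression is named for categorical outcomes.

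For the last three the section mentions no frailty, group random effect or cluster-robust variance.

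The Secondary outcomes section lists peer-supporter characteristics associated with uptake, to be evaluated from the participant and supporter databases together with focus groups and interviews. The Intervention section says "Two peer supporters will be recruited from each cluster in the intervention arm (one male and one female". The control arm has no supporters.

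**The concern.** Arm and support-group characteristics take one value per support group. Members of a group share meetings, talks and, in the intervention arm, the same pair of supporters, so their outcomes are likely to be correlated. The choice of a cluster design and a cluster sample-size formula already concedes this. A Cox or logistic model that ignores the grouping takes its precision from the number of members when the information on these exposures comes from the number of groups. Standard errors are then too small and tests reject too often.

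At stake are the treatment hazard ratio, any arm comparison that moves to the logistic model because of imbalance (a realistic prospect with 14 clusters), and conclusions about which group characteristics go with uptake. The peer-supporter outcome has a separate limit: only seven groups contribute to it, whatever model is chosen.

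**Working it through.** **Inputs from the article.** There are 7 groups per arm with a mean of 50 members. "A 15% loss to follow-up contingency has been built into the sample size calculation", so 50 × 0.85 = 42.5 members per group are followed. The claim is "80% power to detect a two-fold difference in the proportion of PLWD who take up eye exam, with a 5% level of significance". Two-sided testing is assumed, because the article does not say.

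**Inputs not in the article.** Neither the ICC nor the control-arm uptake used for the sample size is stated. The ICC is varied from 0 to 0.10. Where an uptake is needed, 13% is assumed, from the 87% unmet annual need given in the Background.

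**The plan's own figure.** 7 × 50 = 350 per arm and 2 × 350 = 700, as stated. The 80% power cannot be confirmed without the two missing inputs. Assuming 13% v 26%, 145 per arm are needed before clustering. With m = 42.5 and ICC 0.025 the design effect is 1 + 41.5 × 0.025 = 2.04. Then 145 × 2.0375 = 295.4, and 295.4 / 0.85 = 348 per arm. So 350 is attainable, and under that assumption it implies an ICC of about 0.02 to 0.03.

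**Effect of leaving clustering out.** For an exposure constant within groups:

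- design effect: DE = 1 + (m − 1) × ICC
- ratio of unclustered to correct standard error: 1/√DE
- true rejection rate of a nominal 5% test: 2 × [1 − Φ(1.96/√DE)]

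| ICC (assumed) | DE, m = 42.5 | Rejection rate | DE, m = 50 | Rejection rate |
|---|---|---|---|---|
| 0 | 1.00 | 5.0% | 1.00 | 5.0% |
| 0.01 | 1.415 | 9.9% | 1.49 | 10.8% |
| 0.02 | 1.83 | 14.7% | 1.98 | 16.4% |
| 0.05 | 3.075 | 26.4% | 3.45 | 29.1% |
| 0.10 | 5.15 | 38.8% | 5.90 | 42.0% |

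At m = 42.5 the unclustered standard error is 1/√1.83 = 0.74 of the correct size at ICC 0.02, and 1/√3.075 = 0.57 at ICC 0.05.

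**Check by simulation under the null** (m = 50, 13% uptake). An unclustered Cox score test of arm, 7 v 7 groups, rejected 12%, 18%, 23% and 31% of the time at ICC 0.01, 0.02, 0.03 and 0.05. An unclustered z test of a binary trait splitting seven groups 3 v 4 (m = 50) rejected 11%, 17%, 22% and 30%. Both agree with the formula to within about 2 percentage points.

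**Degrees of freedom when the groups are respected.** The arm comparison has 14 − 2 = 12 (critical t 2.18). A characteristic summarised per group over the seven intervention groups has 7 − 2 = 5 (critical t 2.57). With seven points a correlation reaches p < 0.05 only if |r| ≥ 2.571/√(5 + 2.571²) = 0.75, and a true correlation of about 0.89 is needed for 80% power.

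**The case against.** The strongest reply is that the article names model families and leaves variance estimation to fuller documents that are not shown. It is plainly aware of clustering: it commits to the CONSORT extension for cluster trials, sizes the trial with a cluster formula, says it will study effects at individual and cluster level, and names a mixed model for the primary outcome. Time to examination is not among the listed outcomes.

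Much of this stands, and it rules out several stronger readings that a reader might infer:

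- **That the plan treats all 700 members as independent.** The article nowhere says so; that would be an inference from silence.
- **That one inflated error rate is a property of the plan.** The rate depends on an ICC that the article does not give. It also does not carry over in full to individual covariates that vary mainly within groups.
- **That the plan promises significance tests on supporter traits, or proposes supporter sex as a predictor.** It does neither. The regression sentence covers individual and group characteristics, and the supporter outcome draws partly on qualitative data. Any supporter analysis would involve about 350 intervention-arm members, not 700.
- **That every supporter trait has exactly seven independent values.** The article does not say whether the monthly calls are divided between the two supporters. If they are, some traits vary within groups. The limit of seven applies to traits summarised per group.

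What the reply does not remove is that the section goes beyond silence for the arm comparisons. It specifies the baseline adjustment and omits the unit of randomisation. The mixed model does not fill the gap: it is described as repeated-measures, its random-effect level is unnamed, and it covers only the primary comparison.

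**Conclusion.** The point holds in a limited form. The Cox model, the logistic model for imbalance and the regressions on support-group characteristics are named without any allowance for the 14 randomised groups. Fitted that way, they would be anti-conservative for arm and for group-level characteristics: about 10-11% false positives at ICC 0.01, 15-16% at 0.02 and 26-29% at 0.05, from 5% at ICC 0 to about 39-42% at 0.10. These figures rest on an assumed ICC, 42.5 to 50 members per group and two-sided testing.

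Separately, and whatever the unseen documents say, peer supporters exist in only seven clusters (2 × 7 = 14 people). Characteristics summarised per group over those clusters have about 5 degrees of freedom.

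This should be fixed. It does not show that the primary comparison is wrong, because a mixed model is named there and its details may be settled elsewhere.

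**What to change.** In the Statistical analysis section:

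- State that the Cox model will include a shared frailty per support group, or use cluster-robust variance with a small-sample correction suited to 14 clusters.
- State that the logistic model for imbalance and the association regressions will include a support-group random effect, or an equivalent, with small-sample degrees of freedom.
- State that supporter characteristics, and group characteristics summarised over the intervention arm, will be reported as exploratory or descriptive across the seven groups.

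The cost is wording only, with no change to recruitment, data collection or sample size. The price is wider intervals for the hazard ratio and group-level associations, and a peer-supporter result that describes and does not test.
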